#### Sample/data collection

Breast milk sample collection is standardized to reduce bias and potential diurnal variability. Hindmilk is chosen to make a uniform sample across participants, since the constituents of milk change from the start to the end of a feeding. Mothers are being asked to provide 3–5 mL of milk samples that flowed towards the end of a feeding or a breast pumping session between 8 and 9 A.M. Milk samples are being collected in sterile 15-mL plastic tubes and immediately placed in an ice box and transported to the icddr,b laboratory within 4 hours of collection, where they are stored at −80°C in 500-μL aliquots until analysis. Breast milk samples are being collected at <3 d (before supplementation), 7 weeks, and 15 weeks postpartum. Blood samples of 2–3 mL from infants and mothers are being collected at 7 weeks and 15 weeks (Figure 1). A clinic nurse obtains blood samples in heparinized tubes.

During follow-up, field workers use structured questionnaires in paper form to collect data on pregnancy history, anthropometry, demography, diet, morbidity, and time/date of maternal supplementation, infant vaccination, and biological sample collection (Figure 1).

### Laboratory investigations

#### Assessment of breast milk immune components

Breast milk contains an array of bioactive compounds. In this study, we select key immune markers that represent overall functional competence of breast milk and rationalize with infant immune responses. In the anti-microbial and microbial growth regulator categories, we measure secretory immunoglobulin A (sIgA) and soluble cluster of differentiation antigen 14 (sCD14), respectively. In addition to non-specific opsonization of pathogens for phagocytosis and destruction, breast milk sIgA has DNase- and RNase-like activity [23] that could protect infants by hydrolyzing pathogenic viral and bacterial nucleic acids [24]. CD14 participates in inflammatory responses against the lipopolysaccharide (LPS) of Gram-negative infections [25] and also recognizes soluble peptidylglycan from the Gram-positive bacterial cell wall [26]. In the tolerance-priming and anti-inflammatory category, we measure transforming growth factor beta (TGF)-β [27], which specifically enhances IgA production [28] and promotes healing of intestinal cells damaged by infection [29]. In the lymphopoietic and colony-stimulating categories, we will measure interleukin (IL)-7 and granulocyte-monocyte colony-stimulating factor (GM-CSF), respectively. IL-7 is involved in peripheral homeostasis of all major T cell subsets, including naïve [30] and memory [31] cells. GM-CSF is characterized by its ability to stimulate neutrophil, monocyte/macrophage, and eosinophil colony formation. It can also enhance phagocytosis and antibody-dependent cell-mediated cytotoxicity [32].

#### Experimental procedure

Frozen milk samples will be thawed at 37°C and centrifuged at 13,000 rpm for 15 min at 4°C. The upper fatty layer will be removed, and the middle aqueous layer will be extracted by pipette for the measurement of sIgA, sCD14, IL-7, and GM-CSF by enzyme-linked immunosorbent assay (ELISA) kits [33]. Since TGF-β is bound in the fat portion of the milk [34], milk samples will be acidified by the addition of 1 N HCl for 10 min at room temperature followed by neutralization by 1.2 N NaOH/0.5 M HEPES, as described earlier [33].

### Assessment of infant immune functions

#### Innate immune responses

The innate immune system provides the first line of defense against invading microbes. Activation of pattern recognition receptors, such as Toll-like receptors (TLRs), in immune cells leads to the release of immune regulators which have direct antimicrobial activity and can also shape the adaptive immune system. In this study, we assess the cytokine responses to TLR4 and TLR9 stimulation. TLR4 expression on monocytes and neutrophils identifies bacterial LPS, a major outer wall structural component of Gram-negative bacteria. We evaluate inflammatory status by measuring tumor necrosis factor (TNF)-α/IL-10 responses to LPS stimulation. TLR9, preferentially expressed on plasmacytoid dendritic cells, recognizes microbial unmethylated CpG oligodeoxynucleotides (CpG ODN) sequences. We measure type 1 interferon (IFN)-α in response to CpG ODN stimulation. IFN-α plays a key role against virus replication [35] and induces the expansion of cytotoxic T cells [36,37].

#### Experimental procedure

To study innate immunity, 100 uL whole blood (1:1 in 10% autologous plasma containing RPMI-1640) is cultured for 24 hours at 37°C and 5% CO_2_ with TLR4 agonists MPLA (monophosphoryl lipid A, Invivogen)/LPS (Sigma) at 1.0 ug/mL and with TLR9 agonist ODN-2216 (Type A CpG oligonucleotide, Invivogen) at 1 uM. Optimum concentrations of these agonists for culture have been selected from our previous experiments and other studies [6,38,39]. After incubation, cell-free supernatants are collected and stored at -80° with 1% protease inhibitor for the analysis of TNF-α and IL-10 (MPLA/LPS culture) and IFN-α (CpG ODN culture) by ELISA kits.

#### T cell polarization responses

Appropriate adaptive immune responses are required for recovery from normal, childhood infections. For the assessment of adaptive immune competence, we will measure distinct differentiation of T helper (Th) cells into four different subtypes based on expression of signature cytokine in response to mitogenic stimulation. Signature cytokines for Th1, Th2, Th17, and T regulatory (Tr)-1 are IFN-γ, IL-13, IL-17, and IL-10, respectively. The Th1 response promotes defense against intracellular pathogens, while the Th2 response promotes defense against extracellular pathogens and allergic reaction. Th17 cells play important roles in various autoimmune conditions and the progression of tumors. Tr1 cells are an inducible subset of regulatory T cells that play a pivotal role in promoting and maintaining tolerance [40].

#### Experimental procedure

To study epitope-independent T cell mitogen mediated cytokine responses, diluted (1:4) whole blood is cultured with 2 ug/mL SEB (Staphylococcal enterotoxin B, Sigma) for 3 days. After incubation, cell-free supernatants are collected and stored at -80^0^ with 1% protease inhibitor for the analysis of IFN-γ, IL-13, IL-17, and IL-10 by ELISA kits.

#### Vaccine responses

We utilize a novel cell-mediated method for measuring the vaccine-specific antibody response from mononuclear cells termed antibody in lymphocyte supernatant (ALS) culture [41]. Although serum antibody is widely used to assess post-vaccination immunity, it is not possible to distinguish between recently produced antibodies and pre-existing antibodies as a result of previous antigen exposure or from passively derived maternal antibodies. Serum antibodies include the accumulated soluble antibodies, while the ALS assay quantifies only the amount and strength of circulating, antibody-secreting plasma cells from a recent immunization. To obtain these plasma cells, we collect infant blood samples 1 week after the first and 1 week after the third doses of vaccination (Figure 1). After vaccination, antibody-secreting cells in the draining lymph nodes transiently peak and then decline within a few weeks due to selection for higher affinity plasma cells and apoptotic loss of low-affinity cells, and at the same time cells begin to migrate and accumulate in the bone marrow compartment, which remains the predominant site of antibody production [42,43]. Because of the methodological difficulties involved in investigating bone marrow plasma cells, we use the ALS method as described in our previous study [5].

#### Experimental procedure

To study the extent of vaccine-specific antibody-secreting plasma cell generation following single and three doses of immunization, we separate peripheral blood mononuclear cells (PBMCs) using the Ficoll density gradient procedure, and 1 x 10^7^ cells/mL in RPMI-1640 with 10% fetal bovine serum (FBS) are cultured without any stimulation for 3 days at 37°C and 5% CO_2_. Cell-free supernatants are then harvested to determine pertussis toxin and hepatitis B surface antigen-specific IgG responses by commercially available ELISA kits.

#### Assessment of vitamin A status

The vitamin A levels of breast milk and mother and infant plasma will be measured by HPLC [44]. Since vitamin A is associated with milk fat, which varies within the feeding episode, breast milk vitamin A content will be expressed as concentration per gram of milk fat, measured by the creamatocrit method. These methods are now currently in place at icddr,b [45].

### Outcome variables

The primary outcome variables are breast milk immune regulators at <3 d (before supplementation), 7 weeks, and 15 weeks postpartum. These variables are:sIgA, sCD14, TGF-β, IL-7, and GM-CSF, andVitamin A status

The secondary outcome variables are associated with infant immune responses at 7 weeks and 15 weeks of age as a result of maternal postpartum VAS. These variables are:Microbial pattern recognition receptors (Toll-like receptor, TLR) and stimulated TNF-α, IL-10, and IFN-α responses,Epitope-independent mitogen (PHA) stimulated T cell polarization: IFN-γ (Th1), IL-13 (Th2), IL-17 (Th17), and IL-10 (Tr1),Pertussis toxin and hepatitis B surface antigen-specific IgG antibody-secreting plasma cell responses after single dose (at 7 weeks) and multiple doses (15 weeks) of vaccinations, andPlasma vitamin A.

Other variables include mother’s plasma vitamin A, infant complete blood count (CBC) including hemoglobin and other red blood cell indices, and infant anthropometry and morbidity data.

### Data management

Data obtained from the field site are being entered into a predesigned database created by using the Epi Info 7 program (developed by the Centers for Disease Control, CDC) for this project. 20% data is checked by independent verification. Laboratory data generated from ELISA are exported directly from the instruments into Excel-compatible data files, while other laboratory data, such as CBC and retinol data, are entered into Excel spreadsheets. All these data will be directly uploaded to the Epi Info project to link with other variables in the database. Paper copies of field site questionnaires and all laboratory assay results are retained as backup.

### Data analysis plan

Statistical analyses will be done in SPSS 17.0 for Windows (SPSS Inc., Chicago, IL, USA). Data analysis will be conducted on intent-to-treat principles. Distributions of study variables will be analyzed to identify outliers and test assumptions of normality and equal variance. Data will be transformed to create normal distributions as needed. Randomization will be checked by evaluating infant sex, mode of delivery, gestational age, birth weight, mother age, BMI, and parity status using the *t*-test for continuous and the chi-square test for categorical variables. These variables will be used as covariates in multiple linear regression models to assess treatment effect on the continuous outcome variable of immune measures. If these adjustments have any considerable impact on the findings, the effect of the adjustment will be reported along with the effect without adjustment to evaluate whether the adjustment process interferes with the randomized comparisons. An interaction term, for example, treatment x postpartum time point of supplementation, will be used in mixed model multivariate analysis followed by inspection of univariate *F*-ratios. Interactions and main effects will be further analyzed for specific mean differences using *post hoc* analyses with a correction of alpha. Effect sizes associated with univariate *F*-statistics will be expressed as eta-squared (η^2^) for providing an indication of variance explained by the main effect or interaction. Effect sizes based on a specific difference in mean will be expressed as Cohen’s *d* for an indication of the magnitude of differences. Bivariate correlation in conjunction with multiple regression analysis will be used to evaluate inter-relationships among different immune measures associated with the effect of VAS.

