#### Sample size calculation

In this study, our primary aim is to compare the mean responses of immune markers in breast milk following postpartum VAS compared with a placebo. There are limited data available with human studies. In one study, supplementing postpartum women with a single 200,000 IU vitamin A dose increased secretory immunoglobulin A (sIgA) concentration in breast milk by 45.7% compared to a placebo within one day [8]. We are interested in determining if at least 20% higher immune markers (including sIgA) in breast milk persist at 4 months among women who receive a single dose of 200,000 IU vitamin A either at <3 d (Group 1) or at 6 weeks (Group 2) postpartum compared to the placebo (Group 4) and 10% higher responses among women who receive two doses of 200,000 IU vitamin A both at <3 d and 6 weeks (Group 3) postpartum compared to single-dosed postpartum women. In a one-way ANOVA design, sample sizes of 29 in each of the four groups achieves 80% power to detect our predicted differences using an *F*-test with 0.05 significance levels. The size of the variation in the means is represented by a standard deviation (SD) of 39.5 mg/dL of sIgA. The common SD within a group is assumed to be 126 mg/dL, a pooled value obtained from a previous trial [8]. There are no data available regarding immune measures of infants resulting from maternal VAS. In this project we consider that lymphocyte antibody responses in infants of the four maternal groups are the prime outcome variables which might link to the protection of infants from infection. With 29 infants per group, we will have >80% statistical power to detect a mean difference of 75% of the population standard deviation at α = 0.05 based on direct comparison between infants of the placebo group and infants of any of the three maternal VAS groups. Considering 10% attrition, our goal is to recruit 32 postpartum women into each of the four groups, for a total of 128 participants.

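### The pre-supplementation milk value is listed as a primary outcome time point and missing from the stated covariates; using it as each marker's baseline would be a free gain in precision

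*Protocol article*

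**What the plan says.** The Outcome variables section states: "The primary outcome variables are breast milk immune regulators at <3 d (before supplementation), 7 weeks, and 15 weeks postpartum". The first of these three samples precedes any supplementation, as the section itself says.

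The Data analysis plan names the baseline characteristics: "Randomization will be checked by evaluating infant sex, mode of delivery, gestational age, birth weight, mother age, BMI, and parity status". It continues: "These variables will be used as covariates in multiple linear regression models to assess treatment effect on the continuous outcome variable of immune measures". No milk measurement is on this list. The Sample/data collection section confirms that milk is taken from each mother before supplementation and again at 7 and 15 weeks.

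A second model is described only in part: "An interaction term, for example, treatment x postpartum time point of supplementation, will be used in mixed model multivariate analysis". Main effects and interactions are then followed up. The one interaction named concerns when the capsule was given, not when milk was sampled.

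The Sample size calculation aims at a late difference: "We are interested in determining if at least 20% higher immune markers (including sIgA) in breast milk persist at 4 months". I read this as the 15-week sample, the last milk collection. It uses a one-way ANOVA with no covariate.

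**The concern.** In a randomized trial, a measurement taken before treatment is a baseline. Listing it as an outcome gives it a role in which it carries no information about the treatment effect. Leaving it off the covariate list withholds the role in which it could help, which is to explain between-mother variation in the later value of the same marker.

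What is at stake is precision. The trial is sized at almost exactly 80% power, with no allowance for baseline adjustment, so any gain would be margin that the design now lacks. There is also an open question of interpretation: with a pre-dose visit among the primary time points and no treatment-by-sampling-visit term named, the text does not rule out a group main effect averaged over a visit at which the true effect is zero.

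**Working it through.** **Inputs from the Sample size calculation.** Four groups; "sample sizes of 29 in each of the four groups achieves 80% power to detect our predicted differences"; "test with 0.05 significance levels"; SD of the group means 39.5 mg/dL; within-group SD 126 mg/dL.

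**Input not in the article.** The within-group correlation r between the <3 d value and later values of the same marker. I assume a range from 0 to 0.7. The seven listed covariates are left out on both sides of each comparison, because the article does not say how much variance they explain.

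**Step 1: reproduce the stated figure.** The noncentrality is λ = 4 × n × (39.5/126)² = 4 × 29 × 0.0983 = 11.40, with 3 and 4 × (29 − 1) = 112 degrees of freedom. Noncentral F power is 80.4%, and 29 is the smallest n that reaches 80%. The stated figure holds for an unadjusted 15-week analysis.

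**Step 2: add the baseline as a covariate.** The residual variance is multiplied by 1 − r², so λ becomes 11.40/(1 − r²), with one denominator degree of freedom fewer (111). The unadjusted n that would carry the same information is 29/(1 − r²).

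| r (assumed) | 1 − r² | λ | Power, 29 per group | Equivalent unadjusted n per group | n per group for 80% power |
|---|---|---|---|---|---|
| 0 | 1.00 | 11.40 | 80.4% | 29 | 29 |
| 0.2 | 0.96 | 11.88 | 82.2% | 30.2 | 28 |
| 0.3 | 0.91 | 12.53 | 84.3% | 31.9 | 27 |
| 0.5 | 0.75 | 15.20 | 91.1% | 38.7 | 22 |
| 0.7 | 0.51 | 22.35 | 98.3% | 56.9 | 16 |

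At r = 0.2, 0.3 and 0.5 the gain over 29 is about 1, 3 and 10 women per group. At r = 0 nothing is gained, and the lost degree of freedom does not show in the power to one decimal.

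**Step 3: the conditional case of averaging over all three visits.** Suppose a group main effect were the mean of the three listed visits, with no effect at <3 d, equal effects at 7 and 15 weeks, equal SDs and a common correlation r. The effect is multiplied by 2/3 and the variance by (1 + 2r)/3, so λ is multiplied by (4/9)/((1 + 2r)/3) = (4/3)/(1 + 2r).

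- r = 0.3: λ = 11.40 × 0.833 = 9.50, power 72.0%.
- r = 0.5: λ = 11.40 × 0.667 = 7.60, power 61.2%.
- For comparison, the mean of the two post-dose visits alone, without baseline, gives 94.7% and 91.1%.

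Below r = 1/6 the multiplier exceeds 1, and the three-visit mean has more power than the 15-week value alone (84.8% at r = 0.1), because averaging also removes noise. The shrinkage to two thirds remains at any r.

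**The case against.** The strongest reply is that nothing here is invalid. Randomization keeps the unadjusted 15-week comparison unbiased, the stated power reproduces, and the outcome list may simply be a sampling schedule: the words in parentheses show that the authors know the first sample is pre-treatment. That stands. The list is nevertheless headed as primary outcomes, and the covariate list is explicit, so both statements deserve correction.

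The size of the gain is also open to challenge. The Background says that the immune composition of milk changes over lactation and that colostrum differs markedly from mature milk in vitamin A. A low r is therefore plausible, and the gain may be only 2 to 4 points of power. This stands too, and is why the gain is given as a range.

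Three stronger readings are tempting, and the article does not support them.

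- A reader might infer that the planned group effect is diluted by one third. That needs a main effect averaged over visits that include <3 d. The article neither prescribes nor excludes this: its interaction is given only as an example, and a model with a group-by-visit term could properly keep baseline as a visit. Leaving baseline out of the covariates does not by itself dilute anything.
- A reader might infer an inflated type I error from the reporting rule: "If these adjustments have any considerable impact on the findings, the effect of the adjustment will be reported along with the effect without adjustment". Inflation would require choosing the more favorable of two results. The rule reports both, for the stated purpose of checking whether adjustment disturbs the randomized comparison. What it leaves open is which model is primary.
- A reader might extend the point to the infant outcomes. Infant blood is drawn only at 7 and 15 weeks, so no pre-dose value exists there.

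**Conclusion.** The point holds as a free improvement, not as an error that invalidates the analysis. A pre-treatment measurement is given the role of a primary outcome time point and is left out of the covariates, where it could add precision. With 29 per group, baseline adjustment of the 15-week value would raise power from 80.4% to 82.2%, 84.3% or 91.1% at r = 0.2, 0.3 or 0.5. These figures rest on the article's own SDs, an assumed r that may be at the low end or below, and a linear relation on a suitable scale.

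The drop to 72% (r = 0.3) or 61% (r = 0.5) is conditional on averaging a group effect over the pre-dose visit. It is a reason to exclude that analysis in words, not a description of what is planned.

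**What to change.** For the breast milk outcomes only:

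- Describe the <3 d value as baseline and remove it from the primary outcome time points.
- Make the 15-week value primary, in line with the 4-month target of the sample size calculation.
- Add the same marker's <3 d value, suitably transformed, to the listed covariates, or use it as a constrained baseline (equal group means before treatment).
- In repeated-measures models, use only the 7- and 15-week visits as outcomes, with a group-by-visit term, and state that no group effect is averaged over the pre-dose visit.
- Name the baseline-adjusted model as primary and always report the unadjusted result as a sensitivity analysis, whether or not the two differ.

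The cost is plan wording and one degree of freedom per model. No sample, visit or recruit is added. The Trial status section says that stored frozen milk is analyzed only after follow-up ends, so at the stage the article describes, the change can be made before any milk results exist.

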## Discussion

During early life, an infant is not capable of producing immune regulatory factors sufficient for an adequate host defense. Breast milk bioactive compounds can compensate for the developmental delay of the recipient immune system by providing necessary support at the mucosal or systemic sites. We hypothesize that high dose VAS during the postpartum period would improve immune regulatory factors of breast milk and consequently improve infant immune status in geographical settings where the prevalence of vitamin A deficiency is very high. However, the concentration of vitamin A in breast milk is highest in the first 3 weeks postpartum, that is, in the colostrum in the first week and in the transitional milk in the next 2 to 3 weeks [46]. Following this period, well-nourished mothers usually have stable vitamin A concentrations during the lactation [47], while deficient mothers may have breast milk with lower concentrations [46]. However, if the mother cannot meet the increased vitamin A requirements during lactation through diet, her body attempts to compensate by drawing on the vitamin A reserves in the liver [48]. Thus, maternal dietary intake is an important determinant of breast milk vitamin A concentrations and an infant’s vitamin A status [46,49]. Considering this, we anticipate that data from Group 2 mothers in our study, who receive a single 200,000 IU vitamin A supplement at 6 weeks postpartum, may show higher breast milk immune components than data for Group 1 mothers, who receive the same dose supplement at <3 d postpartum. This prediction is supported by the observation that maternal supplementation with 400,000 IU within 24 hours postpartum does not improve breast milk status at 3 or 6 months [50]. However, a study that used a 300,000 IU dose at 1 to 3 weeks postpartum reported improved breast milk retinol concentrations at 6 to 9 months postpartum [51], indicating that a postpartum period of supplementation is important for breast milk retinol status. However, high dose VAS results in an immediate increase in circulating retinol concentration in plasma and breast milk that takes 3 to 4 weeks to equilibrate with liver storage. Considering this biological phenomenon, we predict that women in Group 3, who receive a second dose of vitamin A 6 weeks after the first dose (total: 2 x 200,000 IU), would have more sustained vitamin A stores and thus more breast milk immune components.

To our knowledge, this is the first placebo-controlled randomized clinical trial of postnatal VAS to investigate the key bioactive compounds in breast milk, important for infant immunity, in relation to dose and time point of postpartum supplementation and whether such maternal supplementation improves infant immune status during the critical period of early infancy when the infant experiences adaptation to both non-pathogenic and pathogenic organisms. Specifically, characterizing the adaptive immune responses in infants following the vaccination schedule, we will be able to evaluate the duration and nature of immune competence against infections in general. Time points for maternal supplementation are selected based on convenience. Mothers who visit health facilities or hospitals for delivery usually stay 3 to 4 days after normal delivery with longer stays for cesarean delivery. Another opportunity for the mothers to visit the clinic is 6 weeks postpartum in order to start immunization for their babies under the national infant immunization program. Our study results would help policymakers to consider postpartum VAS programs without introducing any additional visits by the mothers.

Our study does not aim to determine the impact of postpartum VAS on morbidity or mortality, which would require larger sample sizes and population-representative samples. Our prime goal was to undertake inclusive analysis of immune parameters in breast milk and infant blood samples, and for pragmatic reasons, we restricted our catchment area to one urban maternity clinic, from which blood samples could reach the icddr,b laboratory within 3 to 4 hours of collection. The prevalence of vitamin A deficiency among pregnant women in that area is known to be high and similar to that in rural areas in Bangladesh [52,53], but considering disease burden and environmental factors, urban and rural settings might differ. Enrollment at the maternity clinic rather than in the community did not skew our study subjects towards higher socio-economic status, since this public maternity clinic provides maternal and child care at highly subsidized rates or at no cost.

In summary, the ongoing study is an effort to understand the biological rationale for the potential effect of postpartum vitamin A supplementation with appropriate doses and postpartum time points to ensure adequate vitamin A and bioactive compound supply in breast milk to meet an infant’s optimum immune development as well as the daily vitamin A requirement.

